## Abstract

**Background:**

In the UK, one in four patients are in work at the time of their hip or knee replacement surgery. These patients receive little support about their return to work (RTW). There is a need for an occupational support intervention that encourages safe and sustained RTW which can be integrated into National Health Service practice. We developed a two-arm intervention trial, based on a feasibility study, to assess whether an occupational support intervention (the OPAL (Occupational support for Patients undergoing Arthroplasty of the Lower limb) intervention) is effective in supporting a reduced time to full, sustained RTW compared with usual care in patients undergoing hip and knee replacement.

**Methods and analysis:**

This is a multicentre, individually randomised controlled superiority trial comparing the OPAL intervention to usual care. 742 working adults listed for elective primary hip or knee replacement, who intend to RTW, will be randomised to the OPAL intervention or usual care. The intervention comprises: (1) multimedia information resources; and (2) support from a designated RTW coordinator. The primary outcome is time until ‘full’ sustained RTW without sick leave for a consecutive 4-week period. Secondary outcomes are: time to any RTW, measures of functional recovery, number of ‘sick days’ between surgery and ‘full’ sustained RTW and the use of workplace modifications to facilitate their return. A health economic evaluation and a mixed methods process evaluation will assess cost-effectiveness and the implementation, fidelity and acceptability of the intervention, respectively. Outcomes will be collected at baseline, 3, 6, 9 and 12-month follow-up time points, as well as a monthly RTW questionnaire.

**Ethics and dissemination:**

Dissemination will focus on supporting the wider adoption and implementation of the intervention (if effective) and will target groups for whom the results will be relevant. This trial was approved by West Midlands—Edgbaston REC 23/WM/0013.

**Trial registration number:**

ISRCTN13694911.

STRENGTHS AND LIMITATIONS OF THIS STUDYThe OPAL trial is testing an evidence-based intervention developed as part of earlier National Institute for Health and Care Research funded research (the OPAL feasibility study health technology assessment 15/28/02, ISRCTN27426982).Pragmatic inclusion criteria will allow all patients, in both paid and unpaid work, who intend to return to work (RTW) after surgery, to participate.Embedded process evaluation will ensure issues with implementation and adoption are recognised within the trial and used to refine the RTW coordinator role prior to any wider National Health Service adoption at the end of the trial.There is a training burden and a requirement for clinical time for the RTW coordinator role which will likely impact on trial delivery given existing clinical pressures on elective services.

## Introduction

### Background and rationale

 In the UK, National Institute for health and Care Excellence (NICE) clinical guidance (NG157) recommends that orthopaedic teams discuss and provide information on return to work (RTW) for patients undergoing primary hip and knee replacement.^1^ Despite this, there is substantial variation in the provision of occupational advice and support.^2^ The current ‘standard of care’ is for patients to receive little or no information or support from their hospital orthopaedic team or General Practitioner (GP) to enable RTW.^3^,^6^ Furthermore, fewer than 35% of patients have access to occupational health support at work.^3^,^6^ There is a need for an occupational support intervention that encourages safe and sustained RTW and can be integrated into UK National Health Service (NHS) practice.

Planned surgery to replace a hip or knee joint is a routine NHS procedure that is becoming more common in people of working age. A quarter of UK patients undergoing primary hip and knee replacement are in work at the time of surgery (~50 000/year).^3 7 8^ This proportion will rise over the next decade with an increasing incidence of hip and knee osteoarthritis^9^ and people working longer.^10^ Returning to work is an important indicator of functional rehabilitation and quality of life. Working has physical and mental health benefits and aids recovery after joint replacement.^11^,^13^ Estimates for the mean time to RTW after hip or knee replacement range from 10 to 14 weeks.^314^,^17^ This equates to approximately 4.2 million days of sickness absence related to recovery after surgery at a societal cost of approximately £400 million/year.^3^

Advice from health professionals about the expected time to RTW can influence absence duration. Patients’ expectations of RTW before surgery are a predictor of work outcomes post-surgery. It is therefore important to provide appropriate advice and support to help patients set realistic expectations about their RTW after surgery. Encouraging and supporting RTW through an occupational intervention initiated prior to surgery could help minimise some of the health and socioeconomic consequences of joint replacement surgery. Determinants of RTW are rarely considered when advising patients about hip and knee replacement surgery and their subsequent RTW.^2 4 5^ In a UK survey, only 19% of health professional respondents routinely offered RTW advice to this patient group and <10% used written information or offered onward referral to occupational health services.^2^ There is therefore significant scope to improve current practice in-line with NICE recommendations (NG157).^1^

In 2016, the health technology assessment (HTA) programme funded a feasibility study conducted by our group (HTA:15/28/02).^3^ This study developed an occupational support intervention for working adults initiated prior to elective hip and knee replacement, to improve the speed of recovery to usual activities including work. The OPAL feasibility study used a mixed-methods research design within an intervention mapping framework to develop an occupational intervention to support RTW after hip and knee replacement. The intervention had a strong theoretical background and was underpinned by biopsychosocial methods that supported behavioural change in the target groups (patients, health professionals and employers). It was manualised as a set of patient and health professional performance objectives that defined its content, format, delivery and timing while maintaining pragmatism in the ability of participating sites to administer the intervention alongside usual care.

The OPAL occupational support intervention consists of a suite of multimedia resources that support the patient to develop an individualised RTW and rehabilitation plan tailored to their needs. It involves them in decisions about their care and RTW and provides a framework for their healthcare team to provide support and advice. The intervention also includes an RTW coordinator (RTWC), to facilitate active delivery of each of the elements of the intervention. This aligns with previous studies that demonstrate that the provision of an RTWC is positively associated with time to RTW and the probability of returning to work across a variety of healthcare settings.^18^,^23^ Moreover, a systematic review recommended service coordination as a core component of RTW interventions.^24^

## Aim and objectives

The aim of this trial is to assess whether an occupational support intervention for people undergoing elective primary hip or knee replacement, initiated prior to surgery, is effective in supporting a reduced time to full, sustained RTW compared with usual care and is a cost-effective use of NHS resources.

The objectives are:

Undertake a multicentre, two-arm parallel group randomised controlled superiority trial to determine whether a tailored occupational support intervention initiated prior to elective hip and knee replacement reduces time to ‘full’ sustained RTW.Undertake a 6-month internal pilot to confirm the feasibility of the trial in terms of site set-up, recruitment rate and fidelity of intervention delivery.Undertake an analysis of secondary outcomes.Undertake a cost-utility and cost-effectiveness analysis of the occupational support intervention compared with usual care.Assess the fidelity of intervention delivery and its acceptability to patients, health professionals and commissioners.Develop an implementation plan for delivery of the intervention post-trial (depending on findings).

## Methods and analysis

The OPAL trial incorporates a clinical trial, process evaluation and economic evaluation.

### Trial design

The OPAL trial is a two-arm multicentre, randomised, superiority trial with parallel groups. There will be a 6-month internal pilot and embedded economic and process evaluations. The trial will assess the effect on time to full, sustained RTW of the OPAL occupational support intervention versus usual care in 742 people undergoing elective primary hip and knee replacement in the UK. Participants will be followed-up at 3, 6, 9 and 12 months post-surgery. The participant flowchart can be seen in figure 1. Recruitment is planned to start in April 2023 and finish in July 2024.

**Figure 1 F1:**
[figure not shown]
Overview of trial design and flow of participants through the trial. EQ-5D-5L, Euroqol 5 Dimensions 5 Levels; HTA, health technology assessment; NHS, National Health Service; PROMIS, Patient-Reported Outcomes Measurement Information System; QoL, Quality of Life; RTW, return to work; WLQ, Work Limitations Questionnaire

### Trial setting

A minimum of 14 UK NHS hospitals will participate as study sites. The sites are geographically spread and include several situated within the top decile for UK deprivation. Site selection will be targeted to ensure sampling is from a diverse range of demographic and occupational groups to optimise equality, diversity and inclusion. The study interventions will commence and be delivered in secondary care. There will be interaction with primary care (GP) and commercial (employers) stakeholders as part of the intervention.

### Eligibility criteria

#### Inclusion criteria

Adults aged 16 years or older listed for elective primary hip or knee replacement.In paid or unpaid work.Intend to RTW after surgery.Any hip or knee procedure that is covered by the NICE NG157 guideline and would mandate the completion of a National Joint Registry (NJR) primary hip or knee replacement data form (NJR K1 or H1 form).

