### Outcomes

#### Primary outcome

The primary outcome of the OPAL trial is time until ‘full’ sustained return to any work, defined as work resumption to the same hours as prior to joint replacement, in any role, without any day of sick leave for a consecutive 4-week period.

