#### Secondary outcomes

- Time to any RTW.

- Measures of functional recovery to daily activities and social participation:

Oxford Hip/Knee Score (OKS/OHS)^26 27^—joint-specific, PROMs designed to assess disability in patients undergoing hip (OHS) or knee (OKS) replacement. Each score contains 12 questions scored on a 5-point scale (0–4 points) producing scores ranging from 0 (poor function) to 48 (good function).Lower Extremity Functional Scale (LEFS)^28^—a valid self-reported patient-rated outcome for the measurement of general lower extremity function. It contains 20 questions each scored on a 5-point scale (0–4 points) producing scores ranging from 0 (very low function) to 80 (very high function). It has been shown to have good measurement properties compared with the SF36 and WOMAC scores^29^—WOMAC (Western Ontario and McMaster University Osteoarthritis Index) is disease specific for hip or knees and is scored by the patient. SF36 (Short Form 36 Health Survey Questionnaire) is used to indicate the health status of participant populations.PROMIS social participation short form questionnaires (eg, ability to participate questionnaire, satisfaction with social roles and activities questionnaire, satisfaction with participation in social roles questionnaire)^30 31^—PROMIS (Patient-Reported Outcomes Measurement Information System) is a set of person-centred measures that evaluates and monitors physical, mental and social health. We will use the social health tools developed by PROMIS to measure social participation and satisfaction with participation and social roles.

- Number of ‘sick days’ between surgery and ‘full’ sustained RTW.

- Participant adherence to the intervention and the intervention’s physical rehabilitation programme (including self-reported, 5-point Likert scales (very helpful, helpful, neither helpful nor unhelpful, unhelpful, very unhelpful)).

- Proportion of participants using workplace interventions, adaptations and modifications to facilitate their RTW (eg, changes in working hours and shift patterns, changes to work role or work environment or use of additional equipment within the workplace).

- Health-related quality of life (Euroqol 5 Dimensions 5 Levels (EQ-5D-5L)).^32^

- Work productivity (Work Limitations Questionnaire).^33 34^

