### Sample size

A previous meta-analysis of Randomised Controlled Trials (RCTs) examining work coordination programmes for work disability found an HR for time to RTW of 1.34 (95% CI: 1.14 to 1.56).^23^ With 90% power, 5% alpha, to detect an HR=1.34, assuming a median time to RTW of 3.2 months.^17^ Accounting for 20% attrition, an average of 31 patients per RTWC, intraclass correlation (ICC)=0.01 the sample size required is 742 with equal allocation. A minimum of 12 RTWC would be required to deliver the trial. The sample size was calculated for a log-rank test using PS power and Sample Size software.

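### Eligibility accepts any intended return to work but the primary event needs pre-surgery hours, so 90% power is not secured; stratify the primary analysis by planned hours

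*Protocol article*

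**What the plan says.** All references are to the protocol article.

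- **Inclusion criteria.** The work-related conditions are "In paid or unpaid work" and "Intend to RTW after surgery". Neither mentions hours.
- **Primary outcome.** Full sustained return is "work resumption to the same hours as prior to joint replacement, in any role", and it must be "without any day of sick leave for a consecutive 4-week period". The role may change; the hours may not.
- **Secondary outcomes.** Time to any return to work is listed separately. Workplace modifications that help people return include "changes in working hours and shift patterns".
- **Follow-up and withdrawal.** Monthly return-to-work data stop at the primary event or at 12 months.
- **Sample size.** "With 90% power, 5% alpha, to detect an HR=1.34, assuming a median time to RTW of 3.2 months". The only allowances are 20% attrition and clustering by return-to-work coordinator (31 patients each, ICC 0.01). The result is 742.
- **Data collection.** The pre-surgery work pattern is recorded at baseline. The article does not mention the hours the participant plans to work afterwards.

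**The concern.** Some people who mean to go back to work mean to go back for fewer hours, for example in a phased retirement. They meet the entry criteria. If they keep to the plan they cannot meet the event definition, however early and stable their return. They are not lost to follow-up, so the attrition allowance does not cover them. They stay in the risk set of both arms until month 12.

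This costs more than a few events. As other participants return, those who cannot have the event make up a growing part of each risk set, and a larger part in the arm where return is faster. Hazards are then no longer proportional, and the Cox HR and log-rank statistic move towards no difference. What is at stake is the chance of detecting a useful intervention. Randomisation should balance the group between arms, so allocation bias is not the issue.

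**Working it through.** **1. Inputs.** From the Sample size section: HR 1.34, control median 3.2 months, power 90%, alpha 5%, attrition 20%, 31 patients per coordinator, ICC 0.01, N = 742, log-rank test. From Follow-up and withdrawal: 12 months. Assumed here: two-sided alpha, exponential return times, and an equal share in both arms.

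**2. Reproducing 742.**
- Events (Schoenfeld): 4 × (1.960 + 1.282)² / (ln 1.34)² = 491.
- Event probability by month 12: control 1 − exp(−12 × ln 2 / 3.2) = 0.926; intervention 1 − exp(−1.34 × 12 × ln 2 / 3.2) = 0.969; mean 0.947.
- Participants before inflation: 491 / 0.947 = 518.
- Design effect: 1 + 30 × 0.01 = 1.30 in the intervention arm only, which averages 1.15 over the two arms. The article's minimum of 12 coordinators × 31 = 372, about one arm, fits this.
- N = 518 × 1.15 / 0.80 = 745, close to 742. A design effect of 1.30 in both arms gives 842 and does not reproduce the figure.

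So 742 rests on about 93% and 97% of participants having the event. There is no group that cannot have it.

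**3. Effective size.** 742 × 0.80 / 1.15 = 516, or 258 per arm.

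**4. Reading A: HR 1.34 and the 3.2-month median hold among those who can return to the same hours.** A share p in each arm never has the event and stays at risk to month 12; the rest have exponential times. Simulated two-sided log-rank test, 258 per arm, 6000 trials per value:

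| p | Power |
|---|---|
| 0 | 0.90 |
| 3% | 0.80 |
| 5% | 0.73 |
| 10% | 0.60 |

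The average HR falls to about 1.27 at 5% and 1.23 at 10%. The mechanism shows at p = 5%. By month 12 this group makes up 0.05 / (0.05 + 0.95 × 0.074) = 41% of the control risk set and 0.05 / (0.05 + 0.95 × 0.031) = 63% of the intervention risk set.

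**5. Reading B: HR 1.34 already holds for the whole trial.** Only the event count falls. Events = 516 × 0.947 × (1 − p), and power = Φ(½ × √events × ln 1.34 − 1.96).
- p = 5%: 465 events, power 0.88.
- p = 10%: 440 events, power 0.87.

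**6. Stratifying by the plan recorded before randomisation (reading A).** When the plan predicts the outcome perfectly, stratified log-rank power is 0.89 at 3%, 0.88 to 0.89 at 5% and 0.87 at 10%. When 3% to 10% plan fewer hours but only 50% to 70% of them keep to it, and the others return like everyone else, power is about 0.86 to 0.89. A harsher version holds the share who stay on fewer hours at 3% to 10% and lets still more people plan it. Stratified power is then 0.81 to 0.89, against 0.58 to 0.81 unstratified.

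**The case against.** **The share is unknown.** A reader might infer that the trial does not have its stated 90% power. The article does not support that. It gives no share, 742 reproduces from its own inputs, and at a share of zero power is 90%. This objection stands; what can be said is that the power is not secured.

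**Reading A may not be the plan's.** The article gives HR 1.34 and the 3.2-month median for time to return to work, with no restriction to people able to resume their hours. If 1.34 is the whole-trial HR, the loss is about 1 to 3 points at shares of 5% to 10%. The cited sources are not at hand, so both readings are shown.

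**A plan is not an outcome.** People change their minds, and the same hours in another job count. Only those who actually stay on fewer hours cannot have the event. This stands, and the imperfect-plan runs allow for it.

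**The broad entry and strict endpoint look deliberate.** The article presents pragmatic inclusion as a strength, repeatedly targets full sustained return, and keeps time to any return as a secondary outcome. That is a good reason to leave both definitions alone. It does not give the sample size an allowance for the resulting group.

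**Changed hours may be temporary.** The listed modification ("changes in working hours and shift patterns, changes to work role or work environment") need not mean a permanent cut, and a temporary one only delays the event. It is weak evidence that the endpoint scores good support as failure, and the point does not rest on it.

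**The median.** A reader might infer that the median time to full return would be overstated. It would not: if some participants never regain their hours, a longer median is the correct result for this outcome.

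**Conclusion.** The mismatch is real and lies in text that the article itself fixes. Entry asks for any intended return, the event asks for the same hours, and the sample size has no room for people who satisfy the first and not the second. The stated 90% power holds only if that group is close to empty.

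The size of the loss depends on two things the article does not give: the share, and whether HR 1.34 refers to those who can resume their hours or to everyone. At a 5% share, power is about 0.73 on the first reading and 0.88 on the second; at 10%, 0.60 and 0.87. All figures assume two-sided alpha, exponential times and equal shares in both arms.

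The loss ranges from slight to material, and the remedy is cheap enough to be worth making without knowing which applies.

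**What to change.** Before randomisation, record whether the participant plans to return to the same weekly hours or to fewer. In the Primary outcome paragraph of the statistical analysis section, stratify the Cox model and the log-rank comparison by that answer. Leave the inclusion criteria and the outcome definition unchanged. The answer predates allocation, so allocation cannot influence it. The model already adjusts for baseline covariates, so its HR is conditional on baseline information in any case.

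A sensitivity analysis can be added in which full return means the hours planned before randomisation where these are lower. It should not replace the primary definition, because it answers a different question. Narrowing eligibility to people who plan the same hours would also remove the mismatch, but it restricts a population that was deliberately kept broad.

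The cost is one baseline question and one stratification term. If the full baseline form already asks about planned hours, only the term is needed. There are two limits: the question helps only for participants not yet randomised, and stratification does not help with people who planned the same hours but end on fewer.

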#### Exclusion criteria

Patients undergoing emergency arthroplasty (eg, for trauma).Adults listed for elective ankle replacement.Adults planned to undergo further surgery within 6 months after their joint replacement.Patients listed for bilateral knee replacements.

### Recruitment and informed consent

Potential participants will be identified from the hip and knee replacement waiting lists at each site. Eligibility screening for work status will take place either during the patient’s preoperative assessment clinical appointment or via phone prior to surgery. If a patient is deemed to be ineligible for the trial, the treating clinician will thank the patient for their interest but inform them verbally that they are not able to take part. They will then continue with their usual care. The patient may be informed about the trial in advance of their preoperative assessment clinical appointment where local practices allow for the provision of pre-appointment information. Potential participants will be provided with information about the trial, including a patient information sheet. Patients will have the opportunity to ask questions of the clinical and local research team before consent for the trial is obtained. If the individual wishes to take part in the trial, informed consent will be taken.

Written consent for participation may occur during the clinical appointment, remotely following the clinic (if the patient prefers further time for consideration) or remotely where the patient is identified and approached directly from the surgical waiting list. Participants will be able to provide consent electronically via Research Electronic Data Capture (REDCap), a secure, cloud-based data collection service or they may request a paper form to give consent (online supplemental appendix 1).

